## Abstract

**Background**: Vascular access in emergency departments (ED) is challenging for patients with difficult venous access (DIVA), causing delays and discomfort. Ultrasound-guided techniques may offer improved outcomes, making it crucial to assess their benefits, risks, and the effectiveness of validated identification systems. **Objectives**: To contribute new evidence regarding the effectiveness of validated tools for identifying DIVA and to assess the clinical benefits of ultrasound-guided vascular access in emergency care, and to assess their utility in arterial puncture for arterial blood gas sampling, from now on ABG, within the ED. **Methods**: This study follows the Standard Protocol Items: Recommendations for Interventional Trials (SPIRIT) guidelines for protocol development and the Consolidated Standards of Reporting Trials (CONSORT) guidelines for the conduct and reporting of the randomized clinical trial (RCT). The trial will be conducted in Spain throughout 2025. The study population will consist of 114 subjects with difficult intravenous access (DIVA), identified using the DIVA scale for individuals under 14 years of age and the A-DICAVE scale for adults, along with 80 subjects from the general surgical area (GSA). Participants will be randomly assigned, in a 1:1 ratio, to either the Control Group (CG) (traditional technique) or the Experimental Group (EG) (ultrasound-guided technique). Data collected will include sociodemographic characteristics, procedure-related variables (e.g., time required, human resources, and materials used), as well as pain levels, assessed using validated scales (EVA, FLACC, PAINAD), and overall satisfaction from both patients and healthcare professionals. Ethical approval has been obtained, and the trial will be registered as an RCT through an official clinical trial registry before recruitment begins. **Results**: Expected results suggest ultrasound guidance will significantly improve first-attempt success rates, reduce procedural time, enhance patient comfort, and optimize resource utilization compared to traditional techniques. **Conclusions**: The integration of ultrasound-guided vascular access into routine emergency protocols could enhance patient safety, satisfaction, and procedural efficiency in emergency care settings.

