### Hypothesis and Objetive

The ultrasound-guided puncture facilitates vascular access in patients with difficult vascular conditions, identified using validated scales, who attend emergency departments.

The main objective of this study is to create a protocol for an RCT to compare ultrasound-guided techniques with traditional methods of vascular access in patients with DIVA identified by validated ED scales.

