### 2.4. Sample Size

The sample size calculation will be based on the minimum sample size formula for mean comparison. Considering data from a similar study conducted in other healthcare settings [6] and assuming a minimal detectable mean difference of 0.52 and a variance of 1.64 (“number of attempts” variable), a minimum sample size of 95 participants was obtained. Accounting for a 20% loss rate, the required sample size increases to 114 participants, with 57 in each group.

For the sample size required for arterial puncture, the calculation will follow data from a study by Grandpiere et al. [3], which reported a 34% difference in success rates using ultrasound compared to the traditional technique. To demonstrate a minimum difference of 37% in the first-attempt success rates between the two groups, with an alpha error of 0.5%, 90% power, and accounting for a 20% loss rate, the required sample size is 80 participants, with 40 in each group.

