### 2.6. Statistical Methods

The data will be analyzed using SPSS software, version 22. Initially, normality tests will be performed to assess the distribution, homogeneity, and comparability of the sample, employing kurtosis, skewness coefficients, and the Shapiro–Wilk test. A descriptive analysis will then be conducted using measures of central tendency and dispersion (SD) for quantitative variables, alongside calculations of the median and interquartile range (IQR). Qualitative variables will be expressed as frequencies (n) and percentages (%).

Subsequently, appropriate statistical tests will be conducted to determine whether the hypothesis can be rejected, analyzing relationships between the different variables. For qualitative variables, the Chi-square test will be used, or Fisher’s exact test if values < 5 are observed in the sample. For quantitative variables, Student’s t-test will be applied, or the Mann–Whitney U test in cases where the data do not follow a normal distribution.

In all calculations performed in the study, an alpha error of 0.05 and a beta error of 0.2 will be considered, with a 95% confidence level.

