**Figure 3 nursrep-15-00177-f003:**
[figure not shown]
Ultrasound canalization PIVC. *Transversal Plane. (Own source)*.

**Table 1 nursrep-15-00177-t001:** Steps of the EG ultrasound-guided technique.

Steps of the EG Ultrasound-Guided Technique	
**STEP 1**	Patient identification and procedure explanation.
**STEP 2**	Preparation of necessary materials.
**STEP 3**	Ultrasound-guided examination of the limb to be punctured (RaPeVa): Identification of vessel patency. Identification of nearby structures to prevent injury during puncture.
**STEP 4**	Selection of an appropriate vessel (depth, diameter, and patency): PIVC: Vessel at a depth of <5 mm, with a diameter at least two-thirds larger than the catheter. Avoid areas of joints or bony prominences. ABG: Depth appropriate for the needle used.
**STEP 5**	Preparation of the puncture site: Hand hygiene. Skin disinfection with 2% alcoholic chlorhexidine (2% aqueous chlorhexidine for patients under 2 years old). Non-touch technique.
**STEP 6**	Ultrasound-guided puncture: Appropriate angle based on vessel depth and puncture system. PIVC: Verification of catheter tip placement using ultrasound imaging. ABG: Visualization of the needle inside the artery.
**STEP 7**	PIVC: Verification of catheter patency, placement of an extension system, and catheter fixation with a transparent, semi-permeable dressing. ABG: Arterial blood sample collection, followed by application of pressure at the puncture site for 5 min (10 min for anticoagulated patients).

**Table 2 nursrep-15-00177-t002:** RTC variables. Source: produced by the authors.

RTC Variables	
**Dependent Variables**	**Description**
Type of technique	Arterial puncture, peripheral venous cannulation with short PIVC
Total score on the A-DICAVE scale	From 0 to 10 score in patients below 14
Score in DIVA scale	From 0 to 8 score in patients over 14
Score of every item on the A-DICAVE scale	Score of every item on the scale
Success	Successful result (Yes/No)
Number of attempts	Number of punctures attempts to achieve cannulation
Numbers of nurses attempting	Number of nurses to achieve cannulation
Time taken in the technique	Time in minutes taken for the procedure
Cannulation zone	Pace of insertion of the catheter (hand, forearm, flexure, arm)
Catheter gauge	Measurement in gauges of the used catheter
Pain	EAV scales (oriented patient), FLACC (pediatric patient) or PAINAD (disorientated patient)
Permanence of the vascular access	Permanence time of the catheter

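### No outcome is declared primary in either cohort, while one global hypothesis is tested at alpha 0.05 through an unranked list of outcomes

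*Protocol article*

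**What the plan says.** The hypothesis section makes one general claim, "The ultrasound-guided puncture facilitates vascular access in patients with difficult vascular conditions", with no endpoint attached. The main objective does not supply one either: "The main objective of this study is to create a protocol for an RCT to compare ultrasound-guided techniques with traditional methods".

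Section 2.4 sizes the two cohorts on different variables. PIVC uses number of attempts (mean difference 0.52, variance 1.64). ABG uses first-attempt success ("To demonstrate a minimum difference of 37% in the first-attempt success rates between the two groups"). The error rates behind the ABG calculation are worded "with an alpha error of 0.5%, 90% power, and accounting for a 20% loss rate". Neither variable is called primary there or anywhere else.

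Section 2.6 says that tests across the variables will show whether the hypothesis can be rejected. It assigns test types by kind of variable ("For quantitative variables, Student’s t-test will be applied, or the Mann–Whitney U test", with chi-square or Fisher for qualitative variables) and closes with "In all calculations performed in the study, an alpha error of 0.05 and a beta error of 0.2 will be considered".

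Table 2 lists 16 dependent variables in one block. Number of attempts ("Number of punctures attempts to achieve cannulation") stands beside success, time, pain, satisfaction and baseline scale scores, with no ranking.

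The abstract expects that "ultrasound guidance will significantly improve first-attempt success rates, reduce procedural time, enhance patient comfort, and optimize resource utilization". Number of attempts, the variable on which PIVC was sized, is not in that list.

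**The concern.** A hypothesis without an endpoint, tested through many variables at 0.05 each, can be called confirmed on whichever variable reaches significance. The 5% error rate then describes each single test, not the conclusion that ultrasound works. The Conclusions section says ultrasound-guided techniques should enter standard emergency department protocols if they prove effective, but no section says which result would count as proof. A reader of the final report could not tell a planned confirmatory result from the most favourable of a dozen.

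**Working it through.** The article gives no overall error figure to reproduce, so the check is what its own rule implies.

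**Inputs**
- Alpha per test: 0.05 (section 2.6). Sidedness is not stated; two-sided is assumed.
- Outcomes for PIVC: 16 dependent variables in Table 2, less technique type and three scale-score rows, gives 16 − 4 = 12. These are success, attempts, nurses attempting, time, zone, gauge, pain, permanence, secondary effects, and patient, family and professional satisfaction.
- Outcomes for ABG: 12 less zone, gauge and permanence, assumed not to apply to a single arterial puncture, gives 9.
- Sensitivity count for PIVC: 10, leaving out zone and gauge, which have no direction of benefit.

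**Independent outcomes, no true difference**

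Any false significant result, 1 − 0.95^k:
- k = 12: 46.0%
- k = 10: 40.1%
- k = 9: 37.0%

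False result in favour of ultrasound only. A two-sided 0.05 test gives 0.025 per test in that direction, so 1 − 0.975^k:
- k = 12: 26.2%
- k = 10: 22.4%
- k = 9: 20.4%

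**Correlated outcomes**

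Attempts, success, time, pain and satisfaction would plausibly move together. Test statistics were simulated as √ρ·g + √(1−ρ)·e, with g shared by all outcomes in a cohort and e specific to each, and a cut-off at the 97.5% normal quantile (300,000 simulated trials).

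| Outcomes | Count | ρ = 0.3 | ρ = 0.5 | ρ = 0.7 |
|---|---|---|---|---|
| 12 | either direction | 39.6% | 31.9% | 23.2% |
| 12 | favouring ultrasound | 20.2% | 16.0% | 11.6% |
| 10 | either direction | 35.2% | 28.7% | 21.2% |
| 10 | favouring ultrasound | 17.9% | 14.2% | 10.6% |

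Nine outcomes were not simulated separately. A smaller run of the same kind with 8 outcomes gave 30.2% (ρ = 0.3) and 19.2% (ρ = 0.7) in either direction, so the ABG figures lie between those and the 10-outcome rows.

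**One primary per cohort at 0.05**

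The false-positive chance is 5% in each cohort, and 1 − 0.95² = 9.75% for at least one across both.

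**The two alphas for ABG**

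Section 2.4 gives 0.5% and 90% power; section 2.6 gives 0.05 and beta 0.2 for everything. No baseline success rate is stated, so a range was tried for a 37-point difference at 90% power, two-sided, without continuity correction.
- Alpha 0.05: 32–33 per group before losses at baselines of about 14–16% or 47–49%. This reaches the stated 40 (32/0.8 = 40; 33 × 1.2 = 39.6).
- Alpha 0.005: at least 36 per group at any baseline tried. This exceeds 40 after losses (36 × 1.2 = 43.2; 36/0.8 = 45).

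The stated 80 therefore fits 5% better than 0.5%, but the text does not settle it.

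**The case against.** The strongest reply is that section 2.4 already gives each cohort an implicit lead outcome. PIVC and ABG are separate cohorts with separate sample sizes and data forms, so different lead outcomes are not a contradiction, and the abstract sentence states expectations rather than designating endpoints. Much of this stands. A reader might infer that the sections contradict each other on the main outcome; they do not, and the sized-on variables are the natural primaries. But an implied primary binds no one while section 2.6 tests a general hypothesis through all the variables at one alpha.

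It is also fair that first-attempt success, though not a row in Table 2, can be derived from success and number of attempts. No data are missing.

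The counts of 12 and 9 are a reading of Table 2. Section 2.6 does not say which variables will be compared between groups. Independence gives the higher figures, and Fisher's exact test, being conservative, lowers them further.

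Finally, procedures for secondary multiplicity are commonly left to an analysis plan, and this is a condensed article. That stands, and no particular adjustment is asked for here. The choice of primary outcome is a protocol matter, and the point rests on the rule that section 2.6 states, not on its silence.

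**Conclusion.** The point holds: no outcome is declared primary, and alpha 0.05 applies to all calculations under a hypothesis with no endpoint. For 12 PIVC outcomes, the chance of at least one false significant result is about 46% if independent and 23–40% with correlation 0.7–0.3, against 5%. For 9 ABG outcomes it is about 37% if independent. In ultrasound's favour alone, it is about 26% (12–20% if correlated) and 20%, against 2.5%. Even the lowest PIVC figure in favour of ultrasound, 11.6%, is more than four times nominal. Dropping zone and gauge changes little.

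Two stronger readings should be resisted. A reader might infer that a false benefit is more likely than not. With two-sided tests, the chance of one stays well below one half in each cohort. Pooling all 21 outcomes gives 66% (1 − 0.95^21), but that counts both cohorts, either direction and full independence; in ultrasound's favour alone it is 41% (1 − 0.975^21). A reader might also infer that the plan intends any outcome to carry the claim. It does not say so; it only fails to prevent it.

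The figures assume two-sided tests, the outcome counts above and no true difference on any outcome. This should be corrected, but it does not call for a redesign.

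**What to change.** - Declare one primary outcome per cohort, the one on which it was sized: number of attempts for PIVC, and first-attempt success for ABG, defined as success = yes with number of attempts = 1. Both components are already collected.
- Label all other outcomes secondary and supportive, and state that a conclusion of effectiveness in a cohort rests on its primary.
- Limit the 0.05 sentence in section 2.6 to the two primaries.
- Reconcile alpha and power for ABG between section 2.4 (0.5%, 90%) and section 2.6 (0.05, beta 0.2), and state the sidedness.
- State that the cohorts answer separate questions, so that 5% applies to each, and acknowledge the 9.75% across both.

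The cost is protocol wording, with no change to data collection or conduct. The small downside is that some secondary results can no longer be presented as confirmatory.

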### 2.7. Ethical Considerations

The study has received approval from the Ethics Committee for Research and Medicines (GASAV/2024/60) and consent from the local healthcare management authorities where the study will be conducted. The research will adhere to the ethical principles outlined in the Declaration of Helsinki and the World Medical Association’s six ethical principles for medical research involving human subjects.

The study will comply with the General Data Protection Regulation and Spain’s Organic Law 3/2018 on Data Protection, ensuring the confidentiality and anonymity of all participants. The provisions of Spanish Law 41/2002 on patient autonomy will also be respected, particularly in cases involving children and patients with cognitive impairments.

Participants will be provided with all necessary information about the study via a Participant Information Sheet and a copy of the informed consent form, which will include the contact details of the principal investigator.

## 3. Expected Results

Data from the CG will be obtained using the traditional technique, which involves palpation and visualization of veins following the application of a tourniquet to the selected limb for PIVC and pulse palpation for arterial punctures. For the EG, the ultrasound-guided technique will be employed, beginning with vessel mapping using the rapid peripheral vein assessment (RaPeVa) technique, the identification and measurement of the selected vessel, and an examination of surrounding structures to avoid potential injury. The ultrasound machine available for performing the ultrasound-guided technique will be a SonoSite model M-turbo, together with a 13-6MHz linear transducer. If the practitioner deems it necessary, they may switch techniques, recording the change on the data collection form and accounting for both interventions.

Table 1 shows the steps to be followed for ultrasound-guided punctures in the EG. This table follows European recommendations on the correct indication and use of peripheral venous devices of the WoCoVa [16] and the Osakidetza arterial puncture procedure guide for blood gases in the adult population [29].

Below are images of the visualization of the vessels using ultrasound (Figure 2) and the placement of the PIVC within the selected vein (Figure 3).

The study design does not allow for the blinding of the technique assignment, either for participants or the collaborating nursing professionals. However, an external observer will be responsible for collecting data regarding patient and/or family pain and satisfaction. All data collected will be alphanumerically coded to ensure that analysts remain blinded to the treatment group assignments.

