### 2.5. Randomization of the Sample

Random assignment of participants to the Control Group (CG) and the Experimental Group (EG) will be conducted with a 1:1 ratio using a simple randomization method. Each participant will have an equal probability of being assigned to either group, minimizing bias and ensuring the equitable distribution of characteristics between the groups. To achieve this, a computer-generated random number sequence will be used. Additionally, random permuted blocks will be created to reduce the predictability of the random sequence, while ensuring an equal number of subjects in each group.

Those responsible for carrying out the techniques shall be unaware of the randomization code so that their performance is not constrained.

Details of the sample selection, inclusion criteria applied, and methods used for random assignments to CG and EG will be documented. This will ensure participants’ right to withdraw their data and guarantee the transparency and replicability of the study.

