### 3.2. Data Collection System

The collaborators will be provided with the necessary training for data collecting. To ensure the quality of care and patient safety with respect to the techniques to be developed in the study, the collaborators must be nurses from the service who have received specific training in ultrasound-guided puncture and have a minimum experience in the service of 2 years, thus being considered competent nurses according to Patricia Benner’s model [33].

Collaborators will be provided with a data collection form accessible from the point of care. A separate form will be used for each technique (PIVC or ABG), ensuring that the data are transferred to a dedicated database specifically prepared for the study. The database will record all relevant variables (Table 2).

The study will be coordinated by the principal investigator, attached to the ED of the hospital, who will be responsible for compliance with the protocol, data integrity, and the supervision of the research team.

The governance of the project will be overseen by an Internal Control Committee, composed of members of the emergency department, which will meet quarterly to review study progress, ethical compliance, and adverse events.

The involvement of an external monitoring committee is not foreseen, given the low-risk nature of the study.

All adverse events shall be documented in a specific data collection form (CRF), with details on their nature, severity, duration, treatment required and outcome.

Adverse events will be considered any unanticipated clinical incident temporally related to the venous or arterial puncture procedure, such as: extensive hematoma, local infection, phlebitis, persistent pain, or vascular damage. These events shall be recorded by the investigator immediately after the procedure and during the clinical follow-up of the patient in the emergency department. An intermediate safety analysis will be carried out when 50% of the planned recruitment is reached.

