Secondary effects	Type of effects (extravasation, phlebitis, obstruction, others)
Patient satisfaction	Level of satisfaction (5-point Likert scale)
Family satisfaction	Level of satisfaction of the family (5-point Likert scale)
Professional satisfaction	Level of satisfaction of the professional who applied the technique (5-point Likert scale)
**Independent variables**	**Description**
Age	Years
Gender	Male, female, nonbinary
Reason for the consultation	Reason for the assistance according to nursing record
Emergency zone	Assigned emergency zone
Triage level	Classification SET (I, II, III, IV, V)
Predisposing factors of DIVA	Factors such as addiction, obesity, old age among others
**Procedure variables**	**Description**
Type of technique	Traditional, ultrasound guided
Transducer placement	Longitudinal, transversal, none
**Confusion variables**	**Description**
Medication given	Medication used through the access
Dilution volume	Volume in ml of the medication dilution
Time of administration	Taken time in minutes of the administration
Conscience level	Glasgow scale
Agitation	Yes/No

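### Discretionary switching of technique is to be counted for both interventions, and nothing says which randomised group a switched patient's outcomes belong to

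*Protocol article*

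**What the plan says.** Section 3 (Expected Results) of the protocol article describes the groups by technique, for example "Data from the CG will be obtained using the traditional technique", and then gives the switching rule: "If the practitioner deems it necessary, they may switch techniques, recording the change on the data collection form and accounting for both interventions". No criterion for a switch is given. The same section says that neither participants nor nurses can be blinded.

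Section 3.2 makes Table 2 the list of what the database holds. The only Table 2 variable that separates the two comparators is the procedure variable for type of technique, with values "Traditional, ultrasound guided". No row gives the allocated group, and no row splits attempts into those before and after a switch. Attempts are defined as "Number of punctures attempts to achieve cannulation".

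Section 2.6 names the tests but gives no rule for a switched patient. Two places point to allocation being kept: section 2.5, where "methods used for random assignments to CG and EG will be documented", and section 3, which says "All data collected will be alphanumerically coded to ensure that analysts remain blinded to the treatment group assignments".

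**The concern.** This is a counting rule that the article states, not a detail left for an analysis plan. Read literally, it credits one randomised patient to both techniques. It can also be read as moving the patient to the technique that finally worked, or as counting every puncture under the arm first assigned. These are three different comparisons, and only the last keeps the randomised groups intact.

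The choice matters because switching most plausibly follows failure. A control patient who switches is then one of the harder cases and has already used up attempts. Grouping by technique moves such patients out of the traditional group, or into both groups, so that the groups differ in more than the technique.

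Number of attempts is the variable on which section 2.4 sizes the venous cohort, so the ambiguity falls on a main outcome. It also touches first-attempt success, on which the arterial cohort is sized. That outcome can be derived from Table 2 as success with one attempt. But a patient switched before the first puncture would then score a first-attempt success without the allocated technique having been tried. Finally, a count of attempts up to cannulation has no clear value for a patient who is never cannulated.

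**Working it through.** The plan states no switching rate and no per-attempt success rate, so it has no figure of its own to reproduce here. The nearest anchor is in section 2.4, "assuming a minimal detectable mean difference of 0.52 and a variance of 1.64". All success and switching rates below are assumptions. Attempts continue until success, a patient switches at most once, and differences are traditional minus ultrasound, so a positive value favours ultrasound.

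**Illustration 1.** Success per attempt is 0.50 traditional and 0.75 ultrasound. Only controls switch, with probability 0.5 after each failure from the second on.

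- No switching: 1/0.50 - 1/0.75 = 2.000 - 1.333 = 0.667.
- Share of controls switching: both first attempts fail in 0.25. Half of these switch at once (0.125). The rest try again, fail half the time and face the same choice, a factor of 0.5 x 0.5 = 0.25. Total 0.125/(1 - 0.25) = 0.167.
- Traditional punctures per control: 1 + 0.5 + 0.125/(1 - 0.25) = 1.667.
- Ultrasound punctures per control: 0.167 x 1.333 = 0.222.
- **By allocated arm:** (1.667 + 0.222) - 1.333 = 0.556 (0.55 by simulation).
- **Each technique credited with its own punctures:** traditional 1.667; ultrasound (1.333 + 0.222)/(1 + 0.167) = 1.333; difference 0.333.
- **By final technique:** the 0.833 of controls who do not switch contribute 0.5 x 1 + 0.25 x 2 + 0.278 = 1.278 punctures (0.278 is the sum from the third attempt on), a mean of 1.278/0.833 = 1.533. Switchers contribute 1.889 - 1.278 = 0.611. The ultrasound group's mean is (1.333 + 0.611)/1.167 = 1.667. Difference 1.533 - 1.667 = -0.133.

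**Illustration 2, set near the plan's 0.52.** Success per attempt is 0.45 and 0.59, so the difference without switching is 2.222 - 1.695 = 0.53. Controls switch with probability s after each failure. Let x = 0.55s, T = 1/(0.45 + x) for traditional punctures per control, w = x/(0.45 + x) for the share switching, and U = 1/0.59. Then:

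- by arm: T + wU - U
- own punctures: T - U
- final technique: T - [U + w(T + U)]/(1 + w)

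| s | Controls switching | By arm | Own punctures | Final technique |
|---|---|---|---|---|
| 0 | 0% | 0.53 | 0.53 | 0.53 |
| 0.10 | 11% | 0.47 | 0.29 | 0.09 |
| 0.25 | 23% | 0.40 | 0.01 | -0.32 |
| 0.50 | 38% | 0.33 | -0.32 | -0.69 |

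Simulation of the same model agrees to within 0.01. The final-technique difference is zero when T = U(1 + w), that is x = (0.59 - 0.45)/2 = 0.07, so w = 0.07/0.52 = 13.5% of controls.

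**No true effect.** With 0.50 in both arms and 20% of controls switching, T = 1.6, w = 0.2 and U = 2. By final technique the difference is 1.6 - (2 + 0.2 x 3.6)/1.2 = -0.67, although the techniques are equal.

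**Switching in both arms.** With 0.45 and 0.59 and a 50% chance of switching after failure in each arm, the difference is +0.19 by arm and +0.12 by final technique. The sign does not reverse.

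**The case against.** The strongest reply is that no section sets an as-treated analysis. Patients are formally assigned to groups, and coding the data to keep analysts blind to assignment makes sense only if a coded assignment is linked to each record. Grouping by the open technique variable would defeat that blinding. Table 2 in a condensed article is plainly not a full data dictionary: it has no patient code and no switch field, although section 3 promises coded data and says that the change is recorded. The both-interventions phrase also has a harmless reading, namely that no puncture is lost when the operator switches. Handling of switched patients may be set in an analysis plan that is not shown.

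Most of this stands, and it rules out two stronger readings. A reader might infer that the database holds no randomised arm; the documents show only that Table 2 does not list one. A reader might also infer that the trial will be analysed as treated; the text leaves that open and does not say it. Nor do the documents say that never-cannulated patients are dropped, since Table 2 has a separate success row. The absence of first-attempt success from Table 2 carries little weight, because it can largely be derived.

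The reply does not remove the counting rule itself. That rule is in the article, it has readings that give different results, and no stated text chooses between them.

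**Conclusion.** The point holds as an ambiguity in a stated rule, on the variable that sizes the venous cohort. With 17% of controls switching, the first illustration turns 0.56 attempts by arm into 0.33 or -0.13, depending on the reading. In the illustration set near the plan's own difference, the sign by final technique reverses once about 13.5% of controls switch.

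These sizes rest on assumed success and switching rates and on switching from control to ultrasound only. Section 3 allows a switch either way, and with equal switching probabilities in the two arms the sign held. A reader might take the figures to show that the trial will report a reversed effect. They show only that a reading left open by the text could do so at modest, one-sided switching. The rule should be settled before the data are analysed and preferably before the form is final, because punctures before and after a switch cannot reliably be separated later if the form did not separate them.

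**What to change.** - **Table 2:** list the allocated arm, in coded form, separately from the technique or techniques used.
- **Section 2.6:** state that the main comparison is by allocated arm in all randomised patients, each counted once. Results by technique received are supportive only.
- **Section 3:** replace the both-interventions phrase with a rule that all punctures, before and after a switch and whether or not cannulation is achieved, count under the allocated arm. Reword the attempts row of Table 2 to match.
- **First-attempt success:** define it as success at the first puncture with the allocated technique.

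The cost is one added field and a few sentences, with no extra patients. The downside is dilution: in the second illustration the by-arm difference falls from 0.53 to 0.40 when 23% of controls switch, and to 0.19 when half of failures lead to a switch in both arms. The change concerns counting only. When an operator may switch is a clinical matter and is not addressed.
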